**Discussion:**

Data from this study will be used to identify the feasibility of a combined exercise programme to be implemented in SSc patients, the acceptability of the intervention and the study design, and to determine the effects of exercise on the microvasculature. Overall, this study will provide sufficient data to inform and support a full multicentre clinical trial.

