To our knowledge, the feasibility of a combined HIIT protocol with short intervals (30 s at 100% peak power output and 30 s passive recovery) and a circuit RT programme on SSc patients has not yet been examined. Moreover, the efficacy of exercise on microcirculation in SSc patients constitutes another unexplored element of SS. Therefore, the primary aim of our study would be to investigate the feasibility of exercise in patients with SSc and the secondary aim is to explore the effects of exercise on microcirculation. Our study objectives are (1) to estimate the rates of recruitment and retention for a future definitive trial of a 12-week supervised exercise programme for SSc patients; (2) to estimate the rates of attendance to and compliance with the supervised exercise programme; (3) to assess the tolerance, acceptability and enjoyment levels of the training protocol; (4) to investigate the effects of exercise on microvascular reactivity in the digital area; (5) to identify and quantify the training dose that may induce microcirculatory improvements in SSc patients; (6) to assess the effects of exercise on HRQoL of SSc patients measured through generic questionnaires and interviews; and (7) to conduct post-intervention interviews with patients to explore individual’s experiences of the study’s procedures and exercise programme.

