### Outcome measures

The timeline for the outcome measures will be the baseline measurements, and the 3- and 6-month follow-ups after randomisation.

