### Statistical analysis

The sample size for a feasibility study should be adequate to estimate the critical metrics needed to assess the feasibility of conducting the definitive study, with sufficient precision [34]. The critical metrics are the consent rate (i.e. the proportion of eligible patients who consent to participate and be randomised), improvement in microcirculation and quality of life as well as compliance with treatment, and attrition rates. Fifteen patients in each group (*n* = 30 in total) will provide a sufficiently precise (within 15 percentage points for a 90% confidence interval) estimate of the proportion willing to be randomised, assuming 35–40% intention to be randomised.

The SPSS software (version 23, IBM SPSS, New York, USA) will be used to enter quantitative data and cleaning the data and to carry out missing values imputation and statistical analysis. The descriptive statistics, including mean and standard deviation, will be presented for basic demographics and primary and secondary outcomes of the patients in intervention and control groups. For categorical data, the χ^2^ test will be used to infer on the significant association. Independent and paired samples *t* tests will be used to account for the changes upon the primary and secondary outcomes within the group at pre- and post-exercise intervention but also between the two groups. Kolmogorov–Smirnov and Shapiro–Wilk tests will be used to test the normal distribution of the dependent variable and Levene’s test will be used to test the homogeneity of variances. Pearson’s r will test any relations and interactions between our variables. The qualitative analysis will be performed using framework analysis [35], aiming to describe individuals’ experiences of exercise, searching for common, recurrent patterns but also exploring participant experiences that might explain behaviour and improve advice and services in the future. Data saturation will be achieved when similar themes arise repeatedly and no new themes arise in the interview.

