## Discussion

Digital ischemia is a direct result of RP in SSc patients that adversely affects their HRQoL. The number of incidents that require hospitalisation and, occasionally, digital amputation is not negligible (30%) [2]. There is strong evidence from a wide range of clinical conditions in which vascular disease plays a leading role in their pathophysiology, that exercise, and more specifically HIIT and RT, are able to improve the endothelial vascular function and, thus, to increase macro- and microcirculation. Based on that evidence, we will attempt to implement a combined exercise protocol, primarily assessing its feasibility and, secondarily, its efficacy on vascular tone. The feasibility study will provide important evidence about the effectiveness of supervised exercise training as a complementary treatment to the usual care (e.g. medical treatment) for improving microcirculation in the digital area, physical fitness, functional ability and HRQoL in SSc patients. The findings will inform a future definitive multicenter randomised controlled trial with a larger sample size. We acknowledge that our sample size might be a limitation for the current study but we need to stress that FESS is a feasibility study in a novel area and we will strictly adhere to the pre-defined eligibility criteria to present a consistent and reproducible outcome. Moreover, the ratio between women and men is uneven; however, the women to men ratio in those with SSc is estimated to 5.2:1 in northeast England [36]. Overall, the study is expected to provide valuable evidence for future research with SSc patients.

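### The article calls the effect on microcirculation exploratory in one place and promises evidence of effectiveness in others, which unranked significance tests at 15 per arm cannot support

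*Protocol article*

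**What the plan says.** Feasibility is the primary aim throughout the protocol article. The status of efficacy varies by section:

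- **Background, last paragraph:** "the secondary aim is to explore the effects of exercise on microcirculation".
- **Abstract, Discussion:** the data will be used "to determine the effects of exercise on the microvasculature".
- **Main Discussion:** "The feasibility study will provide important evidence about the effectiveness of supervised exercise training as a complementary treatment to the usual care". The sentence goes on to cover digital microcirculation, fitness, functional ability and quality of life. The same section concedes that the sample size may be a limitation and says the findings will feed a larger definitive trial.
- **Statistical analysis:** independent and paired t tests "will be used to account for the changes upon the primary and secondary outcomes within the group at pre- and post-exercise intervention", and the sentence then adds comparisons between the two groups. Chi-square tests and Pearson correlations are also planned. Gains in microcirculation and quality of life are listed among the critical metrics.
- **Statistical analysis, sample size:** "Fifteen patients in each group" are to give an estimate "within 15 percentage points for a 90% confidence interval" of the proportion willing to be randomised, "assuming 35–40% intention to be randomised". No precision or power is given for any efficacy outcome.
- **Outcome measures:** the time points are "the baseline measurements, and the 3- and 6-month follow-ups after randomisation".

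**The concern.** The exploratory statement and the two stronger ones cannot all describe the same analysis. If efficacy is explored, the tests yield estimates and ideas for the next trial. If effects are to be determined and effectiveness evidenced, the reader will look to the significance tests, and nothing in the article says which of them answers the question.

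Acetylcholine and nitroprusside responses could point in different directions, as could fitness and quality of life. Under the published wording, any one nominally significant result could be offered as the promised evidence and could then shape the definitive trial's choice of outcome and its expected effect. A later analysis plan could rank the contrasts, but it would not change what the article says the study will show.

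**Working it through.** **1. The plan's own figure.** Wald half-width for a proportion: z × √(p(1−p)/n), with z = 1.645 for a 90% interval and n = 30.

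- p = 0.35: 1.645 × √(0.35 × 0.65/30) = 0.143
- p = 0.40: 1.645 × √(0.40 × 0.60/30) = 0.147

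Both are within 0.15. Solving n = z² p(1−p)/0.15² gives 28 and 29. So the stated precision reproduces with n = 30, but it concerns only willingness to be randomised.

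**2. What 15 per arm offers for efficacy.** Two-sample t test, two-sided 5% (an assumption, since the article states no alpha), all 30 patients analysed:

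- Power is 26% for a true difference of 0.5 SD and 56% for 0.8 SD. For 80% power the difference must be about 1.06 SD.
- The observed difference must reach 2.048 × √(2/15) = 0.75 SD to be significant. If the true effect is smaller than that, any significant result overstates it.

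**3. Chance of at least one false positive between arms.** The count is seven outcomes at one visit: the responses to acetylcholine and to nitroprusside (Iontophoresis section), plus the five other secondary domains in the abstract (fitness, functional ability, transcutaneous oxygen, body composition, EQ-5D-5L).

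- Independent tests: 1 − 0.95⁷ = 0.302.
- Equally correlated tests with correlation ρ: 1 − ∫ [Φ((1.96 − √ρ u)/√(1−ρ)) − Φ((−1.96 − √ρ u)/√(1−ρ))]⁷ φ(u) du.

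| ρ | 0 | 0.3 | 0.5 | 0.7 | 0.8 |
|---|---|---|---|---|---|
| 7 tests, one visit | 0.302 | 0.271 | 0.230 | 0.178 | 0.149 |
| 14 tests, both visits | 0.512 | 0.438 | 0.348 | 0.249 | 0.197 |

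Simulated t tests with 15 per arm and ρ = 0.5 gave 0.232 for seven tests, in agreement. The second row applies only if both follow-ups are tested, which the article does not say.

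**4. The within-arm tests are a separate route.** Suppose both arms change by the same amount and exercise does nothing. With n = 15, a paired t test in the exercise arm is significant with probability 19% for a common shift of 0.3 SD (in SD of the change) and 44% for 0.5 SD. Step 3 does not include these tests.

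**The case against.** The strongest reply is that this is a feasibility trial described in a condensed article. Its primary outcomes are recruitment, retention, acceptability and adherence. Microcirculation is already the named secondary aim, and no success rule for efficacy is stated. The choice of agent, charge, visit and testing order is commonly left to an analysis plan. The Discussion concedes the sample-size limit and defers to a larger trial. Some inflation of this kind arises in any trial with several secondary outcomes.

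Much of this stands, and it rules out several stronger readings that a reader might infer:

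- **That the lack of alpha control or a hierarchy is a defect.** A feasibility trial need not adjust for multiplicity, and the detail may sit in a document not shown.
- **That both follow-ups will be tested, so the 14-test figure is the right one.** This would be inferred from the measurement schedule; the t-test sentence speaks only of before and after the intervention.
- **That each iontophoresis charge will be tested.** The charges are described as steps of one delivery protocol.
- **That a chance finding would be reported as an exercise effect.** The article's caveats support only that it could be.

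The reply does not remove the contradiction. The caveat in the Discussion concerns sample size and leaves the effectiveness sentence in place. An unseen analysis plan cannot correct published wording.

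**Conclusion.** The point holds as an inconsistency between label and claim. The article explores an effect in one section, and in two others says it will determine that effect and evidence effectiveness. The support offered is a set of unranked significance tests within and between arms, in a trial sized for something else.

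The size of the risk is about 23% for at least one false-positive between-arm result at one visit, with a range of 15% to 30%. It would be higher if both visits were tested. This rests on an assumed two-sided 5% level, seven outcomes, and an equal correlation of 0.5 (range 0.8 to 0). None of these values is given in the article. The feasibility conclusions are untouched. The matter should be corrected because it governs what the trial may conclude about exercise, but it does not call the design into question.

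**What to change.** - **Statistical analysis:** state that all efficacy outcomes are exploratory and will be reported as between-arm estimates with confidence intervals, and that no claim of effectiveness will rest on statistical significance.
- **Statistical analysis, preferably also:** the sponsor names in advance the between-arm microvascular contrast and the visit of main interest for planning the definitive trial. The choice is the sponsor's.
- **Abstract (Discussion) and main Discussion:** replace the phrases about determining effects and about evidence of effectiveness with: exploratory estimates of the effect, to inform the design of the definitive trial.

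These are changes of wording in three places and need no further patients, visits or data. The article reports recruitment as ongoing, so the label can be set before results are seen. The small downside is that the trial gives up an effectiveness claim, one that its size and planned tests could not carry.

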## Discussion

Digital ischemia is a direct result of RP in SSc patients that adversely affects their HRQoL. The number of incidents that require hospitalisation and, occasionally, digital amputation is not negligible (30%) [2]. There is strong evidence from a wide range of clinical conditions in which vascular disease plays a leading role in their pathophysiology, that exercise, and more specifically HIIT and RT, are able to improve the endothelial vascular function and, thus, to increase macro- and microcirculation. Based on that evidence, we will attempt to implement a combined exercise protocol, primarily assessing its feasibility and, secondarily, its efficacy on vascular tone. The feasibility study will provide important evidence about the effectiveness of supervised exercise training as a complementary treatment to the usual care (e.g. medical treatment) for improving microcirculation in the digital area, physical fitness, functional ability and HRQoL in SSc patients. The findings will inform a future definitive multicenter randomised controlled trial with a larger sample size. We acknowledge that our sample size might be a limitation for the current study but we need to stress that FESS is a feasibility study in a novel area and we will strictly adhere to the pre-defined eligibility criteria to present a consistent and reproducible outcome. Moreover, the ratio between women and men is uneven; however, the women to men ratio in those with SSc is estimated to 5.2:1 in northeast England [36]. Overall, the study is expected to provide valuable evidence for future research with SSc patients.

## Trial status

Recruitment started in January 2018 and is ongoing.

## Abbreviations

ACh: acetylcholine
FESS: Feasibility of Exercise in Systemic Sclerosis
HIIT: high-intensity interval training
HR: heart rate
HRQoL: quality of life
LDF: laser Doppler fluximetry
RP: Raynaud’s phenomenon
RPE: rating of perceived exertion
SNP: sodium nitroprusside
SSc: systemic sclerosis
TcpO_2_: transcutaneous oxygen pressure
VO_2peak_: peak oxygen uptake
